#### Exclusion criteria

inability to understand the content of the sessions, because of insufficient command of the Dutch language.

inability to fill out the questionnaires.

inability (for example: too aggressive) or unwillingness to function in a group.

a psychiatric condition that requires attention first (for example severe depression, PTSS or psychosis).

a combination of IBS and other chronic bowel diseases, as far as they already diagnosed, such as ulcerative colitis, Crohn's disease or coeliac disease.

major surgery to the lower gastrointestinal tract, such as partial or total colectomy, small bowel resection or partial or total gastrectomy.

past or present radiotherapy to the abdomen (eg carcinoma of the cervix).

### Procedure

Cooperating GPs and specialists are asked to give each eligible patient an invitational letter explaining the goal of the study and describing the interventions. The patient fills in the IBS questionnaire to confirm the diagnosis. If the patient is interested in participating in the trial, the GP or specialist hands the patient study information with the Informed Consent letter and a brochure from the government explaining the law and the rights of patients participating in medical research. After confirmation of the intention to participate, the patient is referred to the collaborating psychologist, either in the hospital or in primary care practice. The psychologist checks the in- and exclusion criteria and explains the study. If the patient is willing to participate, she/he signs the Informed Consent letter, completes the questionnaires and sends them, together with the IBS-criteria checklist in a reply-envelope to the investigator. After randomisation the patient is invited to the therapy she/he is randomised to.

### Randomisation

After inclusion, patients are randomly allocated to one of the three treatment conditions by means of a computer-based, six-block random number tables procedure. Because for group treatment six patients are required, the randomisation is done block-wise to prevent prolonged waiting time for the individual patient. The researcher performs randomisation.

### Intervention

Patients will be randomised to one of the three treatment arms.

(a) Individual hypnotherapy is delivered in a series of 6 individual, bi-weekly 45-minute sessions in which patients receive a structured hypnotherapy treatment. The treatment procedure is developed by the investigator ([name]) based on the hypnotherapy protocol for IBS from the research group of [name] in Manchester UK [17]. Basically, hypnotic suggestions are given to normalise motility of the gut and reduce pain and feelings of discomfort. The precise wording is adjusted to the individual patient. Treatment is given by qualified psychologists who are educated as hypnotherapists and specifically trained for the intervention.

(b) Group hypnotherapy is delivered in a series of 6 bi-weekly 60-minute group sessions, with a maximum of 6 IBS patients per group. The group hypnotherapy is based on the same principle as the individual hypnotherapy but is adapted for the group format. Group hypnotherapy will be given by the same psychologists who deliver the individual therapy.

Both individual and group hypnotherapy patients are given homework assignments consisting of CD recorded hypnotherapeutic exercises. Carrying out these exercises takes 15-20 minutes, at least once daily.

(c) Educational supportive therapy is delivered in a series of 6 bi-weekly 60-minute group sessions, with a maximum of 6 patients per group. In the sessions topics are discussed that are of importance to IBS patients, as determined by research [18-22]. The topics include: information about IBS; the role of food and life-regulation and dealing with stress in managing IBS. Homework assignments are given that take about 15-20 minutes per day.

Educational supportive therapy will be performed by nurse practitioners or psychological assistants who are specifically trained for the intervention.

Treatments are carried out according to a detailed therapy protocol in which all sessions are described (verbatim). Therapists receive this verbatim protocol, the CD with the hypnotherapeutic exercises and homework assignments.

All therapists are trained in the protocol they carry out and subsequent treatment is supervised by the principal researcher.

To prevent contamination of groups, therapists giving hypnotherapy will not give educational supportive therapy and vice versa.

### Other treatments during the study

Patients may continue usual care as instructed by their physicians but are asked not to change it during the research, except on doctor's advice. They are free to seek other treatment. This will be recorded in their questionnaire.

### Study parameters/endpoints

As yet, it is not known what makes hypnotherapy an effective treatment. We assume that hypnotherapy has a direct influence on visceral hypersensitivity (pain processing and pain perception [14] and an indirect influence on pain perception through relaxation and changing cognitions. Furthermore, gut motor activity (motility) can be influenced by hypnotherapy [14]. Finally, hypnotherapy can have an effect on psychological factors such as self-efficacy and feelings of depression that can play a role in IBS. Our choice for outcome measures has been influenced by these assumptions.

#### Main study parameter/endpoint

In line with previous conclusions on optimal outcome assessment in trials on functional gastrointestinal disease [23,24], we chose the number of weeks with adequate symptom relief as the primary outcome. This measure addresses weekly symptom improvement in IBS with treatment using a single question ("Did you have adequate relief of IBS-related abdominal pain or discomfort in the past week?") scored on a dichotomous scale (Yes/No). This instrument is a well validated simple outcome assessment for IBS treatment [25] with a positive responder being defined as someone with more than 2 weeks adequate relief per month [26] which has determined to indicate a clinically significant improvement [26].

The first primary outcome is the difference in the percentage of positive responders between group hypnotherapy and group educational therapy. Group hypnotherapy is expected to be substantially more effective than educational therapy.

The second primary outcome is the difference in percentage of positive responders between group hypnotherapy and individual hypnotherapy. Group hypnotherapy is expected not to be inferior to individual hypnotherapy.

#### Secondary study parameters/endpoints

##### Irritable Bowel Syndrome Symptom Severity

IBS symptoms will be monitored using the IBS symptom severity score (IBS-SSS).

The IBS-SSS assesses five features of IBS (pain severity and frequency; abdominal distension; bowel satisfaction; interference with life in general) and their intensity, using visual analogue scales [27]. The IBS-SSS has been validated and its use is recommended in an overview on outcome measures [24].

##### Irritable Bowel Syndrome Quality of Life

Disease-specific quality of life will be assessed using the Irritable Bowel Syndrome Quality of Life scale (IBS QOL) [28]. It has been validated in different populations. This instrument includes 30 items and consists of nine scales (dysphoria; interference with activity; body image; health worry; food avoidance; social reaction; sexuality; relationships; overall scale).

#### Other measurements

##### Psychological symptoms

Psychological symptoms are assessed with the Dutch version of the Symptom Checklist (SCL-90). It was originally published by Derogatis [29] and translated and validated for the Dutch population by Arrindell & Ettema [30] The SCL-90 is a 90-item multidimensional self-report inventory, designed to evaluate a broad range of psychological problems and symptoms of psychopathology. It has 9 subscales: Agoraphobia, Anxiety, Depression, Somatisation, Insufficiency of thought and action, Distrust and Interpersonal Sensitivity, Hostility, Sleeping problems and Psychoneuroticism (total score).

The SCL-90 is an internationally accepted, widely used, questionnaire with good psychometric qualities[29].

##### Dysfunctional cognitions

The Cognitive Scale for Functional Bowel Disorders (CS-FBD) has been developed by Toner [31] and translated with permission from the author by [name]. The CS-FBD consists of 31 items to measure a patient's level of dysfunctional cognitions concerning his or her IBS. It is a valid and reliable scale that can be used as an outcome measure in evaluating the efficacy of psychotherapeutic interventions for functional bowel disorders [31].

##### Self-efficacy

The Self-Efficacy Scale (SES) is a seven-item questionnaire to measure the confidence of patients about their capacity to influence their somatic complaints. It was originally developed for patients suffering from chronic fatigue [32] and adapted with permission of the author by [name] and [name] for patients with IBS.

##### Costs

The Trimbos/iMTA Questionnaire (Tic-P) for costs associated with Psychiatric Illness, measures direct medical costs due to health care utilization during the past four weeks and indirect non-medical costs due to productivity loss during the past two weeks[33]. It can be adapted for other conditions as well and for this study was adapted for IBS.

### Time line and follow-up

Enrolment started May 2011. The inclusion of patients will take approximately two years. After the active treatment period of 12 weeks, all patients will be followed for an additional period of 9 months, to assess the sustainability of the effects of the interventions. The primary outcome will be measured weekly during the first four weeks after finishing treatment and again weekly during four weeks 9 months post treatment. The secondary endpoints will be assessed prior to intervention, immediately after the intervention and at 9 months after finishing the intervention.

### Other study parameters

Patients are given a "CD use" diary in which they can record the number of times they used the CD or did the hypnotherapeutic exercises in the last week. The homework assignments in the educational supportive therapy are not registered separately.

**Table 1 T1:** Overview of assessments.

	Weeks					
**Visit** **(time point)**	**0** **(start of treatment)**	**12** **(end of treatment)**	**12+** **Every 4 week** **(end of treatment + 4 weeks)**	**12+** **Every week** **After treatment**	**52** **(9 months after treatment)**	**52 + 4** **(4 weeks after 9 months)**

Assessments						

IBS-Mode	X				X	

Informed consent	X					

Inclusion exclusion criteria	X					

Demographic data	X					

Status report	X					

Adequate relief			X			X

IBS-SSS	X	X			X	

IBS-QOL	X	X			X	

SCL-90	X	X			X	

CS-FBD	X	X			X	

SES	X	X			X	

TiC-P	X	X			X	

CD-diary		X		X		

### Sample Size Calculation

Assuming an individual hypnotherapy response rate of 57% [2], a maximum acceptable level of difference of 15% between individual and group hypnotherapy, an alpha of 0.05 and power (1-beta) of 0.80, 135 patients are required in both arms of the non-inferiority trial to show that group-hypnotherapy is not inferior to individual hypnotherapy.

Spiller [34], in an overview of 25 randomised controlled trials, states that when the placebo response is plotted against the length of study, placebo response will be maximum of 75% at around 6-8 weeks, falling to 25% at 24 weeks and zero at 12 months. Our follow-up period will be 9 months. To test whether group hypnotherapy is more effective than group placebo therapy, we will have more than sufficient power assuming a placebo-response rate of 25% and a group hypnotherapy response rate of 57% [13] using the proposed 135 patients in both arms. Powering the study for only the comparison between hypnotherapy and the control intervention, would require only 44 patients in both arms assuming an alpha of 0.05, a power (1-beta) of 0.80, a cluster size of 6 patients per therapist and an intra-class correlation coefficient of 0.05. Assuming at least 10% of loss to follow-up, 354 patients need to be included in the study (150+150+54 (placebo-arm)).

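### The non-inferiority size of 135 per arm omits the clustering that the same section assumes for the other primary comparison; under that assumption its power is about 76%, not 80%

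*Protocol article*

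**What the plan says.** The Sample Size Calculation section of the protocol article covers both primary comparisons.

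- **Group versus individual hypnotherapy (non-inferiority).** The inputs are a 57% response with individual hypnotherapy, "a maximum acceptable level of difference of 15% between individual and group hypnotherapy", and "an alpha of 0.05 and power (1-beta) of 0.80". The result is that "135 patients are required in both arms of the non-inferiority trial to show that group-hypnotherapy is not inferior to individual hypnotherapy". No cluster size, intra-class correlation or sidedness is given for this figure.
- **Group hypnotherapy versus control (superiority).** The inputs are 57% against 25%, again with alpha 0.05 and power 0.80, but now with "a cluster size of 6 patients per therapist and an intra-class correlation coefficient of 0.05". The result is 44 per arm.

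The only inflation applied to 135 is for 10% loss to follow-up, which gives 150 per hypnotherapy arm and 354 patients in all (150 + 150 + 54).

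The Intervention section describes group hypnotherapy as "6 bi-weekly 60-minute group sessions, with a maximum of 6 IBS patients per group". It adds that the psychologists who give the individual sessions also give the group sessions, and that hypnotherapists do not give the control therapy. Under Main study parameter/endpoint, the group hypnotherapy arm appears in both primary comparisons.

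**The concern.** Patients treated together in a group share sessions and a therapist, so their outcomes may be correlated. The plan accepts this when it sizes group hypnotherapy against control. When it sizes the same arm against individual hypnotherapy, it counts every patient as independent. If the correlation exists for one comparison, the part that arises within therapy groups exists for the other.

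The non-inferiority comparison sets the size of the trial: 300 of the 354 patients are in its two arms. If its power is below 80%, the risk of failing to show non-inferiority when the two formats are truly equal is higher than the 20% the plan accepts. The alpha also needs a label, because a non-inferiority conclusion depends on whether a 90% or a 95% confidence interval must exclude a 15-point deficit.

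**Working it through.** **Inputs.** All come from the Sample Size Calculation section: response 57% in both hypnotherapy arms (true difference zero), margin 0.15, alpha 0.05, power 0.80, cluster size 6, intra-class correlation 0.05, 10% loss.

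**1. Reproducing 135.** n = (z₁₋α + z₀.₈₀)² × 2 × p(1 − p) / margin².

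- One-sided 5%: (1.645 + 0.842)² × 2 × 0.57 × 0.43 / 0.15² = 134.7, rounded up to 135. This is an exact match with no design effect.
- One-sided 2.5% (two-sided 5%): with 1.96 in place of 1.645 the result is 171.0, rounded up to 172.
- Other two-sided 5% variants (57% against 42% or 72%, with or without continuity correction) give 159 to 187. None comes near 135.

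The step from 135 to 150 is 135 / 0.9 = 150, so the loss allowance uses up the whole inflation and leaves nothing for clustering.

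**2. Design effect from the plan's own inputs.** 1 + (6 − 1) × 0.05 = 1.25.

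**3. Power with 135 analysed per arm.** Power = Φ(0.15 / SE − z₁₋α), with SE² = 0.57 × 0.43 × (DE_ind + DE_grp) / 135 and 0.57 × 0.43 = 0.2451. For the group arm only, SE = √(0.2451 × 2.25 / 135) = 0.0639, and Φ(0.15 / 0.0639 − 1.645) = 75.9%.

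| Clustering | One-sided 5% (90% CI) | One-sided 2.5% (95% CI) |
|---|---|---|
| None | 80.1% | 70.2% |
| Group arm only | 75.9% | 65.1% |
| Both arms | 72.0% | 60.5% |

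**4. Analysed patients per arm for 80% power.**

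- One-sided 5%: 134.7 × (1 + 1.25)/2 = 151.5, so 152 (group arm only); 134.7 × 1.25 = 168.4, so 169 (both arms).
- One-sided 2.5%: 171.0 × 1.125 = 192.4, so 193; 171.0 × 1.25 = 213.75, so 214.

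**5. Sensitivity at one-sided 5%** (group arm only / both arms).

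- Intra-class correlation 0.01: 79.2% / 78.4%.
- 0.02: 78.4% / 76.7%.
- 0.10: 72.0% / 65.1%.
- All 150 per arm analysed, correlation 0.05: 79.6% / 75.9%.

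**6. What 44 says about sidedness.**

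- Two-sided 5%, pooled variance: 35.9 × 1.25 = 44.9.
- Two-sided 5%, unpooled variance: 33.2 × 1.25 = 41.4.
- One-sided 5%, pooled variance with continuity correction: 34.1, rounded up to 35, × 1.25 = 43.75, so 44.

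Both a one-sided and a two-sided calculation can land at or close to 44. The figure does carry the design effect but does not identify the alpha.

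**The case against.** The strongest defence is that the plan defines its cluster by therapist. Hypnotherapists never give the control therapy, so therapist is nested within arm in the superiority comparison and a therapist effect inflates its variance. The same psychologists treat both hypnotherapy arms, so a therapist effect common to both formats tends to cancel in the non-inferiority contrast. On that view a therapist-level correlation may properly enter one calculation and not the other. Individual sessions also have no group of six.

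This has force against the both-arms figure. A design effect of 1.25 in each arm treats therapist effects as independent between arms that share therapists, so 72% is a lower bound and not the expected value. The defence does not remove the group-arm effect: patients in one group share sessions, this happens in one arm only, and nothing in the individual arm offsets it. Six is a maximum; if 135 of 150 are evaluable the mean group size is about 5.4, the design effect 1 + 4.4 × 0.05 = 1.22, and power 76.4%, which is hardly different.

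Two stronger readings may tempt a reader.

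- **That alpha 0.05 is one-sided for non-inferiority and demonstrably two-sided for superiority.** The documents do not show this. The 44 can be reached from a one-sided calculation as well, so the defect is only that sidedness is not stated.
- **That true power is 60 to 65%.** This follows only if non-inferiority is judged on a 95% interval. The article mentions no such interval, and the choice may be fixed in the full protocol or analysis plan. One-sided 5% is a permissible choice and is the one that 135 matches.

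**Conclusion.** The point holds for the omitted clustering. The article itself states the size, alpha, power, cluster size and correlation, and these do not agree across two comparisons that share an arm, so this is not detail left to another document. Under the plan's own assumptions, power for non-inferiority is about 76% at one-sided 5%, and the chance of missing true equivalence of the formats is about 24% in place of 20%. With both arms clustered and no cancellation the figures are 72% and 28%.

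This rests on 57% response in both arms, 135 analysed per arm, and the whole correlation of 0.05 acting within groups of six. If part of that correlation is a therapist effect common to both formats, or if the true value is nearer 0.01, the loss is smaller (power about 79% at 0.01). The arithmetic behind 135 is correct for what it assumes; the unclustered assumption is what needs correcting.

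**What to change.** In the Sample Size Calculation section:

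1. Carry the design effect of 1.25 for the group arm into the non-inferiority calculation, and restate the power with 135 analysed per arm as about 76%, falling to 72% if the individual arm is clustered too. The sizes that would give 80% (152 to 169 analysed per arm) can be shown for reference.
2. State that 135 rests on a one-sided 5% alpha, that is, a 90% confidence interval compared with the 15-point margin. Note that a 95% interval would lower power to about 65% (61% with both arms clustered).
3. State whether the superiority test is one-sided or two-sided, from the record of the calculation and not by inference from 44.

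The cost is text only, with no extra patients. The stated power becomes less favourable.

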### Recruitment

The 354 patients are recruited in primary and secondary care.

Primary care: Assuming an estimated mean incidence of IBS in primary care in 8 of every 1000 patients, 20 newly diagnosed patients per practice per year and an expected inclusion rate of 25%, 30 general practitioners, each referring 5 patients each year, will be able to refer the total required number of patients (354) in 2,5 years.

Secondary care: The estimation of the number of consultations for IBS in gastroenterology practice, varies between 20-70% of all referrals per year. Using a conservative estimate, about 25% of all referrals will be because of IBS. Thus, in a normal gastroenterologist's practice of a general hospital, with 500 new patients for each gastroenterologist each year, there will be 125 new IBS patients each year. Assuming that 10% of the patients will be interested in taking part in the trial, each gastroenterologist can refer 12 patients a year. Therefore 10 hospitals with at least 2 referring specialists to cooperate in this study for 1,5 years (354 patients) are needed.

Ten hospitals and four primary care psychological practices (working with several referring GPs), in different parts of the Netherlands, have agreed to collaborate in the trial. This ensures that the study population will be representative of the whole Dutch population.

When combining the expected referral rates from the primary and secondary care practices, two years of recruitment will be sufficient to attain the required number (354) of participants.

### Statistical analysis

#### General remarks

All statistical analyses will be based on the intention-to-treat principle, i.e. patients will be analysed according to their initial assignment to one of the randomisation arms.

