### Design

The study is designed as a comparative and a non-inferiority 12-weeks single blind controlled parallel-group trial. The trial will involve IBS patients in primary and secondary care, who will be randomly allocated to either 6 sessions of individual hypnotherapy, 6 sessions of hypnotherapy in group format, or 6 sessions of educational supportive therapy in a group format (control condition) (Flowchart Figure 1). Starting May 2011, the inclusion of patients will take approximately two years, with a follow-up of nine months.

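### The primary non-inferiority comparison of group with individual hypnotherapy rests on intention-to-treat alone, which can be anti-conservative for the effect in treated patients

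*Protocol article*

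**What the plan says.** The Design section sets up a trial with two aims: "The study is designed as a comparative and a non-inferiority 12-weeks single blind controlled parallel-group trial". Under Main study parameter/endpoint, the second primary outcome is the difference in responder percentage between the two hypnotherapy formats, with the expectation that "Group hypnotherapy is expected not to be inferior to individual hypnotherapy". The Sample Size Calculation section sizes the two hypnotherapy arms for this comparison. It takes a 57% response to individual hypnotherapy, "a maximum acceptable level of difference of 15% between individual and group hypnotherapy", alpha 0.05 and power 0.80, which gives 135 per arm and 150 after loss to follow-up.

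The only analysis population is fixed in General remarks: "All statistical analyses will be based on the intention-to-treat principle", which the article explains as analysis by the arm first assigned. The sections that follow describe subgroup analyses and adjustment for baseline differences. None describes an analysis by adherence for the non-inferiority comparison.

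Two further statements bear on adherence. Under Other treatments during the study, patients are asked to keep their usual care unchanged unless a doctor advises otherwise, but "They are free to seek other treatment", and this is recorded. Other study parameters provides a diary of CD use. Session attendance is not in the table of assessments.

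**The concern.** Superiority and non-inferiority respond differently to dilution. If some patients in both arms attend few sessions or rely on outside treatment, their outcomes tend to converge. In a superiority test this costs power. In a non-inferiority test it pulls the observed difference inside the margin and so can help the claim.

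The Discussion part of the abstract says that, if efficacy does not differ, the group form could reach more patients at lower cost. The Conclusion names implementation as the next aim. A mistaken non-inferiority finding would therefore bear directly on practice. Under the rule as written, a reader could not tell whether the two formats are close because group hypnotherapy works as well or because too few patients in either arm received the treatment.

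**Working it through.** **Inputs from the protocol article (Sample Size Calculation).** Response to individual hypnotherapy 57%; group hypnotherapy also 57% (stated for the comparison with control); margin 15 points; alpha 0.05; power 0.80; 135 per arm; loss to follow-up at least 10%; control response 25%.

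**Assumptions.** The article gives no adherence rates. The shares of effectively untreated patients, d_I (individual) and d_G (group), are assumed. These patients are assumed to respond at 25%, borrowing the control rate.

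**Step 1: the plan's own figure.** n = (1.645 + 0.842)² × 2 × 0.57 × 0.43 / 0.15² = 134.7, so 135 per arm, as stated. This takes alpha as one-sided 0.05; one-sided 0.025 gives 172. Then 135 / 0.90 = 150, also as stated. The check below therefore uses one-sided 5%.

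**Step 2: equal non-adherence.** Put the effect in treated patients at the margin, 57% v 42%. The rates by assignment are

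- individual: p_I = 0.57(1 − d_I) + 0.25 d_I
- group: p_G = 0.42(1 − d_G) + 0.25 d_G

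The chance of a claim is Φ[(0.15 − (p_I − p_G)) / SE − 1.645], with SE = √[p_I(1 − p_I)/135 + p_G(1 − p_G)/135].

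| Untreated in each arm | p_I v p_G | Difference | SE | Chance of claim |
|---|---|---|---|---|
| 0% | 57.0% v 42.0% | 15.0 points | 0.0602 | 5.0% |
| 10% | 53.8% v 40.3% | 13.5 points | 0.0602 | 8.1% |
| 20% | 50.6% v 38.6% | 12.0 points | 0.0601 | 12.6% |
| 30% | 47.4% v 36.9% | 10.5 points | 0.0598 | 18.6% |

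For example, at 20%: (0.15 − 0.12)/0.0601 − 1.645 = −1.145, and Φ(−1.145) = 0.126.

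With 150 per arm the last three figures are 8.3%, 13.2% and 19.7%. Varying the response in untreated patients from 0% to 57% moves the results by about one point or less.

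**Step 3: unequal non-adherence, 135 per arm.**

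| Untreated, individual v group | Difference | Chance of claim |
|---|---|---|
| 5% v 10% | 15.1 points | 4.8% |
| 10% v 20% | 15.2 points | 4.7% |
| 5% v 15% | 15.95 points | 3.6% |
| 10% v 30% | 16.9 points | 2.5% |
| 10% v 15% | 14.35 points | 6.2% |
| 20% v 30% | 13.7 points | 7.7% |
| 20% v 10% | 10.3 points | about 19% |

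A sufficient excess in the group arm removes or reverses the inflation. A small excess, or one in the individual arm, does not.

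**Step 4: power of a per-protocol analysis.** With 150 randomised per arm and both true rates at 57%, power = Φ[0.15/√(2 × 0.57 × 0.43/n) − 1.645].

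| Excluded | n per arm | Power |
|---|---|---|
| 10% | 135 | 80.1% |
| 20% | 120 | 75.9% |
| 30% | 105 | 70.9% |

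**The case against.** A reader might infer that intention-to-treat always biases this comparison towards no difference. The article does not support that. It gives no adherence rate for either arm, and step 3 shows that intention-to-treat can be conservative. The defensible statement is that it can be anti-conservative.

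The rise above 5% also counts as error only if the target is the effect in patients who receive the therapy. For the effect of assignment, a diluted difference of 10.5 to 13.5 points really is inside the margin. Whether group therapy can be offered more widely is arguably a question about assignment, and non-attendance caused by the group format belongs to that effect. This stands, and it is why intention-to-treat should stay.

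It can also be said that the article defines intention-to-treat only as analysis by initial assignment, and that an unseen full protocol or analysis plan may hold a per-protocol set. That is possible, so one cannot conclude that no such analysis will be done. But the published rule is phrased to cover every analysis, including a primary non-inferiority test. It is a stated choice rather than a detail left open.

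Nor is other treatment simply permitted: changes to usual care are discouraged. Excluding patients who seek other treatment would be selection after randomisation. If patients doing badly in the worse arm seek help more often, removing them flatters that arm and again favours non-inferiority. Finally, the calculation presumes a test against the margin, whereas the analysis section names only a chi-square test of differences. That is a separate matter.

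**Conclusion.** The point holds in a limited form. Intention-to-treat is the only population the article fixes for its primary non-inferiority comparison, and for the effect in treated patients this can be anti-conservative. With equal non-adherence of 10% to 30%, the chance of a claim at the margin is about 8% to 19% instead of 5%. With clearly more non-adherence in the group arm it can be 5% or lower.

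These figures rest on assumed shares, an assumed 25% response in untreated patients and a one-sided 5% test. They show what could happen and do not forecast this trial. Intention-to-treat is not invalid here, and the sample-size figure for this comparison is not in error on this point. What is lacking is a second view showing whether the conclusion depends on adherence. The change should be made, but the trial does not fail without it.

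**What to change.** - Keep intention-to-treat for superiority and as one of the analyses for non-inferiority.
- For group against individual hypnotherapy, add a per-protocol analysis against the same 15-point margin. Define the set before outcome data are examined, based mainly on the number of the six sessions attended, and log attendance in both arms.
- Do not exclude patients from that set for seeking other treatment. Handle other treatment, as recorded in the questionnaire, in a separate sensitivity analysis.
- Report the intention-to-treat and per-protocol results side by side, and regard non-inferiority as robust only if they agree.

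The cost is one extra analysis and an attendance log. Per-protocol power is about 80%, 76% and 71% if 10%, 20% and 30% of the 150 per arm are excluded. Keeping 135 per arm in that set at 20% or 30% exclusion would need 169 (135/0.80) or 193 (135/0.70) randomised per arm. The per-protocol set is also open to selection bias, so it supplements intention-to-treat and does not replace it.
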